## Withdrawal of individual subjects

It is a prospective cohort study in which the patients are included after informed consent. Subjects can leave the study at any time for any reason if they wish to do so without any consequences.

# SAFETY REPORTING

## Temporary halt for reasons of subject safety

In accordance to section 10, subsection 4, of the WMO, the sponsor will suspend the study if there is sufficient ground that continuation of the study will jeopardise subject health or safety. The sponsor will notify the accredited METC without undue delay of a temporary halt including the reason for such an action. The study will be suspended pending a further positive decision by the accredited METC. The investigator will take care that all subjects are kept informed.

## AEs and SAEs

### Adverse events (AEs)

Adverse events are defined as any undesirable experience occurring to a subject during the study. All adverse events reported spontaneously by the subject or observed by the investiga­tor or his staff will be recorded.

### Serious adverse events (SAEs)

Not applicable. .

## Follow-up of adverse events

All AEs will be followed until they have abated, or until a stable situation has been reached. Depending on the event, follow up may require additional tests or medical procedures as indicated, and/or referral to the general physician or a medical specialist.

SAEs need to be reported till end of study within the Netherlands, as defined in the protocol.

# STATISTICAL ANALYSIS

The principle investigator (HL) has final responsibility with regard to the data. Incidence of objective and subjective nerve damage will be expressed as absolute numbers and percentages. Distance from trocar to nerve will be expressed in absolute numbers.

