# STUDY DESIGN

A explorative single-center prospective cohort study (n=25) at the Radboud University Medical Centre in Nijmegen.

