# METHODS

## Main study parameter/endpoints

- To assess postoperative nerve damage on ultrasound.
  - - Pre- and postoperative ultrasound to identify and measure the intercostal and subcostal nerves (precise location and cross sectional area (CSA) measurement)
- To measure the distances of the subcostal nerve to trocar positions.
  - - Postoperative measurement of distances (in mm) to trocar positions after marking of the nerve

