## Study procedures

All patients will be approached at the outpatient clinic by [name] (researcher) after the decision is made to perform PRA, explaining the study and its procedures. They will be given additional written information including a consent form. If the patient gives informed consent and has no exclusion criteria, he/she will be included in the trial.

Preoperatively:

1. Preoperative questionnaires: (cross-sectional), duration: in total ± 15 minutes.

- Mc Gill Pain questionnaire (Dutch Language version) (5 minutes)
- Hypoesthesia questionnaire (5 minutes)
- Pain Catastrophizing Scale questionnaire (5 minutes)
- Physical examination (5 minutes)

Intraoperatively:

1. After positioning in jack-knife position, an ultrasound is performed by a clinical neurophysiology research technician with measurement of the intercostal / subcostal nerve (see scan-protocol below). Nerve locations are captured with photography. Since the objective of this explorative study is to identify nerve damage after trocar placement and surgery and to see if the current surgical technique needs improving, surgeon is blinded for the results of preoperative ultrasound measurements to reduce bias.

2. PRA will be performed using the normal, clinically and scientifically validated surgical technique.

3. After wound closure a tegaderm foil is applied over the wound. Then repeat measurement of intercostal / subcostal nerve is performed to assess nerve damage / oedema. The distance of subcostal nerves to trocar locations (shortest distance to nerve, in mm) is measured. Again this is captured with photography. Surgeon is blinded for these results as well to prevent bias in future procedures. After this a sterile drape is applied.

Postoperatively after 6 weeks:

1. Postoperative questionnaires: (cross sectional), duration: in total ± 15 minutes.

- Mc Gill Pain questionnaire (Dutch Language version) (5 minutes)
- Hypoesthesia questionnaire (5 minutes)

2. Physical exam by clinical neurophysiology research technician to evaluate dermatomas and subtle neurological injury

3. Repeat ultrasound measurement of intercostal / subcostal nerve to assess nerve damage if neurological injury is present.

Ultrasound protocol:

- Equipment: Sonoside Xporte ultrasound system with linear 5-16Mhz probe, using preset “zenuwecho S”.

- Positioning of patient: jack-knife (see image below)

[figure not shown]

- Scan-protocol:

- Depth: 6cm, gain 60-70%

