## Primary and secondary study parameter(s)

| Study parameters/endpoints | **Presentation of data**  **(quantitative/qualitative)** |
| --- | --- |
| Base-line characteristics | Quantitative |
| Per- and postoperative data | Quantitative |
| Ultrasound parameters | Quantitative |
| Measurement of distance to nerve | Quantitative |
| Postoperative questionnaires | Quantitative |
| Cutaneous hypoesthesia, hypoesthesia, asymmetry abdominal wall after medical examination | Quantitative |

#

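### Section 7 summarises nerve damage and trocar-nerve distance separately and plans no analysis relating the two, although both are primary

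*Protocol*

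**What the plan says.** The protocol names two primary quantities, in the Summary, Section 2 and Section 5.1: postoperative nerve damage on ultrasound, and the distance from the subcostal nerve to the trocar positions.

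- **Damage.** Section 5.1 measures nerve location and CSA before and after surgery in the same patient. Section 7 then says: "Incidence of objective and subjective nerve damage will be expressed as absolute numbers and percentages".
- **Distance.** Section 5.3, on the measurement after wound closure: "The distance of subcostal nerves to trocar locations (shortest distance to nerve, in mm) is measured". Section 7 then says: "Distance from trocar to nerve will be expressed in absolute numbers".
- **Presentation.** The table in Section 7.1 contains the row "Ultrasound parameters | Quantitative", with no summary statistic.
- **Purpose.** Section 5.3 describes the aim as finding nerve damage after trocar placement and surgery, and "to see if the current surgical technique needs improving".
- **Associations.** The only one named (Summary, Sections 2 and 5.2) is between symptoms and ultrasound damage. None involves distance.

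The study is described as explorative, with n=25 (Section 3).

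**The concern.** If a trocar injures the nerve, injury should be more frequent where the trocar passes close to it. Distance and damage are recorded in the same patients, so the data can be examined for this pattern. Section 7 instead reports the two in parallel: how many nerves were damaged, and how far away the trocars were. Neither summary shows which distances belong to the damaged nerves.

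At stake is the part of the stated purpose that concerns trocar placement. The incidence of damage says whether there is a problem, but not whether proximity has anything to do with it. An association sought only after the data have been seen would also carry less weight than one written down beforehand, because the choice of distance, of CSA summary and of trocar would then be open.

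**Working it through.** The protocol gives no alpha, power, effect size or standard deviation, so there is no figure of its own to reproduce. The calculations below are illustrative and assume two-sided alpha 0.05 and 80% power.

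**1. Can separate summaries show the link?** Take 25 hypothetical distances of 2, 4, ..., 50 mm (mean 26, median 26, SD 14.4 with divisor n) and 5 damaged nerves. The point-biserial correlation is r = (mean distance damaged - mean distance undamaged) / SD × √(p(1-p)), with p = 5/25 = 0.2, so √(0.2 × 0.8) = 0.4.

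| Damaged nerves | Incidence | Median distance | Mean distance, damaged / undamaged | r |
|---|---|---|---|---|
| 5 closest | 5/25 = 20% | 26 mm | 6 / 31 mm | (6 - 31)/14.4 × 0.4 = -0.69 |
| 5 furthest | 5/25 = 20% | 26 mm | 46 / 21 mm | (46 - 21)/14.4 × 0.4 = +0.69 |

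The Section 7 output is identical in both rows.

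**2. How many damaged nerves might there be?** The protocol gives no ultrasound damage rate. As an assumed proxy, the Introduction gives symptom rates of 8% (published chronic hypoesthesia), 10% (pain, own centre) and 21% (dullness, own centre).

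- Expected among 25: 25 × 0.08 = 2.0; 25 × 0.10 = 2.5; 25 × 0.21 = 5.25.
- Probability of none, (1-p)^25: 12.4%, 7.2% and 0.3%.
- Exact (Clopper-Pearson) 95% intervals: 3/25 = 12% (2.5% to 31.2%); 5/25 = 20% (6.8% to 40.7%).

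**3. What could an added analysis detect?**

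- *Distance against continuous CSA change.* By Fisher z, the detectable r = tanh((1.960 + 0.842)/√(n-3)). For n=25 this is tanh(2.802/4.690) = 0.54; for 20 usable pairs it is 0.59. With the Spearman variance 1.06/(n-3), it is about 0.55 at n=25, and the 95% limits around zero are tanh(±1.96 × √(1.06/22)) = ±0.41.
- *Distance in damaged against undamaged patients.* The detectable difference by noncentral t is 1.80 SD with 3 damaged and 22 undamaged, and 1.46 SD with 5 and 20.
- *Continuous against yes/no.* In a simulation with an assumed latent correlation of -0.5 (5,000 runs per rate), power was about 75% with the continuous CSA change. With damage as yes/no it was 29% at a 10% damage rate and 41% at 21%.

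**4. Precision of the paired CSA change.** The half-width of the 95% CI for the mean change is t(0.975, 24)/√25 = 2.064/5 = 0.41 SD of the change.

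**5. Is a 6-week CSA change available in everyone?** Section 5.2 lists the 6-week ultrasound without condition. Section 5.3 performs it only if neurological injury is present. Under Section 5.3, a mean 6-week change would come from a selected subset. The post-closure measurement is not affected.

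**The case against.** The strongest reply is that the study promises no such analysis. Section 2 lists visualising the nerve, measuring distance, assessing damage, and correlating symptoms with damage. The Summary and Introduction leave any change of technique to the future. Mapping where the nerve lies is a legitimate descriptive aim, and the frequency of damage also bears on whether the technique needs improving. This stands: the gap is between the stated purpose in Section 5.3 and the stated analysis, and no listed objective is broken.

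Second, a reader might infer that the plan throws away the paired CSA measurements by reducing them to a count. The documents do not support that. Section 7.1 lists ultrasound parameters as quantitative data, separately from the incidence of damage. The within-patient change is unspecified, not excluded, and its details could sit in an analysis plan that is not shown.

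Third, a reader might infer that measurement error would fill the damage count with false positives. That needs a CSA cut-off, and the protocol proposes none; the Introduction speaks of visible injury such as direct lesions and oedema. No false-positive rate can be derived from the documents.

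Fourth, 25 patients will not settle the question, and injury in a few patients may hardly move a cohort mean. Both are true. They are reasons to label the analysis exploratory and to keep the damage counts, not reasons to leave the link unexamined.

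**Conclusion.** The concern holds in a limited form. Section 7 fixes two separate summaries, and nothing in the protocol relates them, so the planned report cannot distinguish opposite distance-damage patterns. That conclusion rests on the text and on the constructed example in step 1; it needs no assumed damage rate.

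The gain from adding the analysis is real but modest. At n=25 only a strong association, r of about 0.54, would be found with 80% power, and r of about 0.59 if only 20 nerves yield a pair. A yes/no comparison resting on some 2 to 5 damaged nerves is weaker still. These figures assume two-sided alpha 0.05, symptom rates standing in for ultrasound damage, and one value per patient. It would go too far to conclude that the study fails its objectives, or that the added analysis would show whether trocar placement should change. The result would be hypothesis-generating.

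**What to change.** In Section 7, add a short pre-specified analysis, labelled exploratory:

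1. Relate each patient's smallest trocar-nerve distance to the paired subcostal CSA change (post-closure minus preoperative), with a Spearman correlation and its 95% CI.
2. Describe that smallest distance in patients with and without ultrasound damage, and with and without a 6-week deficit.
3. Use one distance per patient, so that several trocars in one patient are not treated as independent.
4. Report the post-closure minus preoperative CSA change with a 95% CI alongside, not in place of, the damage counts, and give the counts exact 95% intervals.
5. State that n=25 can show only a strong association, so the result generates hypotheses.

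Do not plan a mean 6-week CSA change until Sections 5.2 and 5.3 are reconciled on who has the 6-week ultrasound.

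The cost is a few sentences and a little more analysis, with no new patients, visits or procedures. The drawback is an imprecise estimate, which the interval will make plain.

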## Primary and secondary study parameter(s)

| Study parameters/endpoints | **Presentation of data**  **(quantitative/qualitative)** |
| --- | --- |
| Base-line characteristics | Quantitative |
| Per- and postoperative data | Quantitative |
| Ultrasound parameters | Quantitative |
| Measurement of distance to nerve | Quantitative |
| Postoperative questionnaires | Quantitative |
| Cutaneous hypoesthesia, hypoesthesia, asymmetry abdominal wall after medical examination | Quantitative |

#

# ETHICAL CONSIDERATIONS

## Regulation statement

This study will be conducted according to the principles of the Declaration of Helsinki (version, date, see for the most recent version: www.wma.net) and in accordance with the Medical Research Involving Human Subjects Act (WMO) and other guidelines, regulations and Acts. The data are handled confidentially and anonymously. All subjects will receive a code. Only the study coordinator has access to the source data and the key to the code. When necessary the subject can be identified through contact with the study coordinator. The data will be kept for 15 years after termination of the study. All handling of personal data shall comply with the Dutch Person Data Protection Act (“de Wet Bescherming Persoonsgegevens Wbp”).

## Recruitment and consent

All patients will be approached at the outpatient clinic by [name] (researcher) after the decision is made to perform PRA, explaining the study and its procedures. They will be given additional written information including a consent form. If the patient gives informed consent and has no exclusion criteria, he/she will be included in the trial.

## Benefits and risks assessment

There are no risks. The burden for the patients is small, due to a longer narcosis (estimated 10 minutes) and extra examinations (ultrasound, physical examination, questionnaire) after 6 weeks (estimated 20 minutes).

## Compensation for injury

The sponsor/investigator has a liability insurance, which is in accordance with article 7 of the WMO.

# ADMINISTRATIVE ASPECTS, MONITORING AND PUBLICATION

## Amendments

Amendments are changes made to the research after a favourable opinion by the accredited METC has been given. All amendments will be notified to the METC that gave a favourable opinion.

## Annual progress report

The sponsor/investigator will submit a summary of the progress of the trial to the accredited METC once a year. Information will be provided on the date of inclusion of the first subject, numbers of subjects included and numbers of subjects that have completed the trial, serious adverse events/ serious adverse reactions, other problems, and amendments.

## Temporary halt and (prematurely) end of study report

The investigator/sponsor will notify the accredited METC of the end of the study within a period of 8 weeks. The end of the study is defined as the last patient’s returned questionnaire and/or visited hospital for medical examination.

The sponsor will notify the METC immediately of a temporary halt of the study, including the reason of such an action. In case the study is ended prematurely, the sponsor will notify the accredited METC within 15 days, including the reasons for the premature termination.
Within one year after the end of the study, the investigator/sponsor will submit a final study report with the results of the study, including any publications/abstracts of the study, to the accredited METC.

## Public disclosure and publication policy

The authors have nothing to disclose.

# RISK ANALYSIS

Not applicable.

